### Randomization and allocation

2.4

The randomization sequence has been generated using a central randomization system. The randomization procedure was programmed using SAS 9.2 software to generate the randomization sequence. In this study, stratified block randomization was designed with airflow limitation severity (GOLD I and GOLD II) as the stratification factor. The researchers use a centralized randomization system to perform participant allocation. Participants are allocated to either the treatment or control group in a 1:1 ratio. The statistical unit maintains centralized control over all study identifiers (center numbers, sequence assignments, randomization codes, and drug numbers) to preserve blinding and prevent bias.

### Blinding

2.5

This is a double-blind trial, and the blinding and unblinding processes are conducted by independent unblinded personnel in accordance with the standardized double-blind trial procedures. These measures ensure that the investigators, relevant research staff, and participants remain blinded to the treatment assignments. The test drug and placebo are designed to match as closely as possible in terms of appearance, smell, and other physical characteristics. All drug packages are prepared according to double-blind standards, ensuring that no distinguishing features on the outer packaging reveal the treatment groups. An independent unblinded staff member, who is not involved in the trial, is responsible for the drug allocation. A documented record of the blinding process is maintained and securely stored for verification. This trial employs a central randomization system for emergency unblinding rather than paper-based unblinding letters. Emergency unblinding is permitted only in critical situations in which the investigator deems it necessary to take urgent measures to ensure patient safety. In the event of unblinding, the date, time, and justification are promptly documented. Additionally, any associated adverse events must be recorded according to the trial protocols.

### Sample size calculation

2.6

The sample size has been calculated using PASS software (Version 15.0.5) based on a superiority test design, with assumptions derived from prior subgroup analyses of *Cordyceps militaris* capsules in the treatment of COPD. The primary endpoint is the change in the post-bronchodilator FEV_1_, with an assumed mean difference of 110 mL between groups, and standard deviations set at 250 mL for the treatment group and 201 mL for the control group (Shergis et al., 2019). A one-sided superiority test is conducted with α = 0.025 and Power = 1-β = 0.90, assuming equal allocation between groups. The sample size calculation indicates that 68 participants per group (N = 136) are required to detect the specified treatment effect. To accommodate an anticipated 15% attrition rate, the final sample size is increased to 160 participants (80 per group).

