Modern pharmacological studies have identified multiple bioactive compounds in *Cordyceps militaris*, including cordycepin, polysaccharides, ergosterol, and mannitol, which exhibit various physiological effects such as immunomodulation, antibacterial and anti-inflammatory activity, and antitumor properties (Olatunji et al., 2018). In a multicenter randomized controlled trial, treatment with *Cordyceps militaris* capsules for 24 weeks increased FEV_1_ by 140 mL in mild-to-severe COPD patients, compared to a 10 mL decrease in the Bailing capsule group (Li et al., 2025). Notably, in the mild-to-moderate COPD subgroup, *Cordyceps militaris* capsules improved post-bronchodilator FEV_1_ by 86 mL versus a 41 mL decline in the control group (*P* < 0.05). Although the study lacked placebo control and used acute exacerbation events as the primary endpoint, the findings remain promising.

Therefore, this study is designed as a multi-center, double-blind, placebo-controlled randomized trial to evaluate the efficacy of *Cordyceps militaris* capsules versus placebo in improving post-bronchodilator FEV_1_ in mild-to-moderate COPD, and will provide evidence for a TCM intervention for preserving lung function in patients with mild-to-moderate COPD.

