### Statistical analysis

2.11

The analysis will be performed using the intention-to-treat principle on the full analysis set, with additional analyses conducted on the per-protocol set and safety set. Only authorized study personnel will be able to view and manage data. The between-group comparison of acute exacerbation frequency will be conducted using a Poisson regression model that includes treatment group as the independent variable, annualized exacerbation rate as the dependent variable, and stratified randomization factors as adjustment covariates. Least squares means with corresponding 95% confidence intervals (with appropriate transformations when required) will be estimated from the specified model to evaluate between-group differences. Continuous variables will be analyzed using appropriate parametric (two-sample t-test or adjusted t-test) or nonparametric (Wilcoxon rank-sum test) methods, while categorical variables will be evaluated using either Pearson’s chi-square test or Fisher’s exact test. Time-to-event endpoints will be analyzed using Kaplan-Meier methodology, with median event times and interquartile ranges (IQR, 25th-75th percentiles) estimated for each group. Between-group differences will be assessed using log-rank tests. For missing data, the last observation carried forward method will be employed for imputation. For the center effect analysis, continuous variables will be analyzed using analysis of covariance or meta-analysis, while categorical variables will be assessed using Cochran-Mantel-Haenszel statistics.

Baseline demographic and clinical characteristics, including age, sex, disease duration, smoking status, smoking index, medical history, and concomitant medications, will be summarized descriptively and assessed for balance between groups. When appropriate, adjusted analyses will be conducted by including these variables as covariates in multivariable models to reduce the impact of potential confounding factors on treatment effect estimation. In addition, prespecified subgroup analyses stratified by sex will be performed to explore potential differences in treatment response to *Cordyceps militaris* capsules.

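### 68 per group gives 80% power for 110 mL on the protocol's own inputs, not the stated 90%, which needs 91 per group

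*Protocol article*

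**What the plan says.** All the inputs are in the protocol article, section 2.6 (Sample size calculation). The calculation is for the primary endpoint and takes a 110 mL advantage of the capsules over placebo. Variability differs by arm: "standard deviations set at 250 mL for the treatment group and 201 mL for the control group". The error rates are also explicit: "A one-sided superiority test is conducted with α = 0.025 and Power = 1-β = 0.90, assuming equal allocation between groups". The result follows: "The sample size calculation indicates that 68 participants per group (N = 136) are required to detect the specified treatment effect". Allowing for 15% attrition, the total is raised to 160, or 80 per group.

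Two other places bear on the point. Section 2.11 (Statistical analysis) names two-sample t-tests, adjusted t-tests or the Wilcoxon rank-sum test for continuous variables. The Introduction reports that in the mild-to-moderate subgroup of the earlier trial the "capsules improved post-bronchodilator FEV_1_ by 86 mL versus a 41 mL decline in the control group", a contrast of 86 − (−41) = 127 mL.

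**The concern.** The article prints a complete set of inputs and an output that does not follow from them. The gap is about a quarter of the required number, far beyond rounding or the choice of formula.

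This is the article's only power statement for the primary endpoint. If it is wrong, the type II error at 110 mL is about 20% with 68 evaluable per group, or about 14% with 80, rather than 10%. A non-significant result could then be given more weight against a 110 mL benefit than the design supports. Section 2.12 (Quality control) gives the data monitoring committee a role in sample size re-estimation, and it would start from a wrong baseline.

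**Working it through.** **Inputs** (section 2.6): difference δ = 110 mL; SDs 250 and 201 mL; one-sided α = 0.025 (z = 1.960); power 0.90 (z = 1.2816); 1:1 allocation. No superiority margin, covariate adjustment or baseline correlation is stated.

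Sum of variances: 250² + 201² = 62,500 + 40,401 = 102,901.

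**Attempt to reproduce the stated 68.** Normal approximation, per group:

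n = (z₁₋α + z₁₋β)² × (σ₁² + σ₂²) / δ² = (1.960 + 1.2816)² × 102,901 / 110² = 10.507 × 102,901 / 12,100 = 89.4, so 90.

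With the noncentral t distribution (Welch, unequal variances), 90 per group gives 89.9% and 91 gives 90.2%, so 91 are needed. The pooled t-test also gives 91. The stated 68 is not reproduced: 68/91 = 0.75.

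**Power at the planned sizes**, δ = 110 mL. The standard error is √(102,901/n).

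| n per group | SE (mL) | δ/SE | Power (Welch t) | Difference detectable with 90% power |
|---|---|---|---|---|
| 68 | 38.9 | 2.83 | 80.1% | 127 mL |
| 80 | 35.9 | 3.07 | 86.2% | 117 mL |
| 91 | 33.6 | 3.27 | 90.2% | 110 mL |

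**What would give 68?** Two combinations of the article's own numbers fit:

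- *110 mL at 80% power.* Normal: 7.849 × 102,901 / 12,100 = 66.7, so 67. Welch t: 67 gives 79.5% and 68 gives 80.1%, so exactly 68.
- *127 mL at 90% power.* Normal: 10.507 × 102,901 / 127² = 10.507 × 102,901 / 16,129 = 67.04, so 68. Welch t needs 69, but power at 68 is 89.98%.

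**What does not give 68** (110 mL, 90% power):

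- one-sided α of 0.05: 73 (normal) or 74 (t);
- two-sided α of 0.025: 106 (normal);
- common SD of 201, 225.5 or 250 mL: 72, 90 or 110 (t).

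A positive superiority margin would only raise n.

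**Attrition step.** 68/0.85 = 80 per group, 160 in total: correct. The fault lies only in the combination of 68, 90% and 110 mL. Starting from 91, 91/0.85 = 107.06, so 108 per group and 216 in total.

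**The case against.** The strongest reply is that the 20% type II error is the pessimistic end. Section 2.11 analyses the full analysis set by intention to treat and fills missing values by last observation carried forward, so the number analysed may be close to 80 per group rather than 68. That stands as far as it goes: power would then be up to 86%, and the fair statement is a range of 80% to 86%. It does not rescue the 90%, which is missed even with no attrition, and carried-forward values could dilute the effect.

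A second reply is that the article does not show which input is wrong. That also stands. Besides the power or the difference, an SD may be misprinted, or a variance reduction left out. For 68 per group to reach 90% at 110 mL, an adjusted analysis would have to remove about 24% of the variance (normal approximation). The calculation mentions no such adjustment, and section 2.11 offers covariate adjustment only where appropriate. The two reconstructions of 68 also use different formulas, so neither is proof of what was entered in PASS.

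The literature citation beside the SDs cannot be assessed without the source. It is not part of this finding and does not affect the arithmetic.

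**Conclusion.** The concern holds. On the stated inputs, 68 per group gives 80.1% power for 110 mL, and 86.2% if all 80 per group are evaluable; 90% requires 91 evaluable per group. The statement is wrong as printed, whichever input was misreported, and it must be corrected.

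These figures take the printed difference, SDs, one-sided alpha and equal allocation at face value, with an unadjusted t-test and roughly normal data. If the true PASS input was 127 mL, 68 per group does carry about 90% power for that difference, but power at 110 mL remains 80%.

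**What to change.** Retrieve the PASS output and make the sample size, difference, SDs and power agree in section 2.6. With N = 160 kept, one of two corrections applies:

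- If 110 mL was intended, state that 68 evaluable per group give 80% power, and 80 per group give 86%, for 110 mL with SDs of 250 and 201 mL at one-sided α = 0.025.
- If 127 mL was the input, state 127 mL and add that power at 110 mL is 80% with 68 per group.

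If the output shows a different SD or an adjusted analysis, print that input and give the power that follows from it.

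The cost is one corrected paragraph and a less favourable power figure, with no extra patients. If 90% power at 110 mL is a firm requirement, the alternative is 108 per group (216 in total) at 15% attrition, which is 56 more participants than planned. Section 2.3.1 expects recruitment to run to late 2026, so the sponsor would have to make that choice while recruitment is still open.

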### Interventions

2.7

Treatment group: Participants in the treatment group receive *Cordyceps militaris* capsules [brand name: Ke Cai], produced by Jilin Zhongsheng Pharmaceutical Co., Ltd., for 24 weeks (four capsules per dose, three times daily).Control group: Patients in the control group receive *Cordyceps militaris* placebo capsules, produced by Jilin Zhongsheng Pharmaceutical Co., Ltd., for 24 weeks (four capsules per dose, three times daily).

Under the supervision of their respiratory physicians, participants may continue pre-existing regimens of long-acting anticholinergics or long-acting β_2_-agonists, either as monotherapy or in combination with glucocorticoids. However, other respiratory drugs are prohibited, such as theophylline, corticosteroid monotherapy, antibiotics, mucolytics, and antitussives (Wu et al., 2014). For acute symptom relief (e.g., clinically significant dyspnea or respiratory distress), salbutamol sulfate metered-dose inhalers may be used as needed. Acute exacerbations are managed according to guidelines, including measures such as controlled oxygen therapy, antibiotics, bronchodilators, and systemic corticosteroids. All exacerbations require documentation of temporal characteristics (onset and offset), precipitating factors, and pharmacological interventions. If emergency medications are required within 6 h prior to a scheduled visit, the visit window may be extended to ensure lung function test validity.

In principle, the use of TCM and patent medicines other than the study drug, including any dosage form, is not allowed after enrollment. If an acute exacerbation occurs, the trial drug should be continued without concomitant TCM whenever possible. If TCM is necessary, detailed records must be maintained in the combined medication record form. For patients with comorbidities (such as hypertension, diabetes, etc.), the original regimen for combined medications can be maintained. During the follow-up period, if any TCM or Western medicine is used, detailed records should be kept. All combined medications must be recorded in detail. Unused study medication should be returned.

### Outcomes and measurements

2.8

The time points of the study data collection for outcome measurements are shown in Table 1.

The primary outcome is change in the post-bronchodilator FEV_1_. Lung function assessments are performed once each at baseline, weeks 12, 24, 36, and 48. Secondary outcomes include additional lung function parameters, such as pre-bronchodilator FEV_1_, pre- and post-bronchodilator measures of FVC, FEV_1_/FVC ratio, mid-expiratory flow (MMEF), forced expiratory flow 75% (FEF75) and forced expiratory flow 50% (FEF50). In addition, frequency of acute exacerbations, time to the first acute exacerbation, COPD Assessment Test (CAT), Cough and Sputum Assessment Questionnaire (CASA-Q), EuroQol five-dimension five-level questionnaire (EQ-5D-5L), and Modified Medical Research Council dyspnea scale (mMRC) are also included. These outcomes are also measured once each at baseline, weeks 12, 24, 36 and 48.

Blood, sputum and stool samples are collected from at least 60 participants enrolled in the Guangzhou center for metagenomics (airway and intestinal flora), transcriptomics, metabolomics, proteomics analyses and induced sputum cell classification. Biological samples are collected at baseline, weeks 24 and 48 after treatment, following standard operating procedures for acquisition, processing, and cryopreservation.

### Safety assessments

2.9

Safety assessments include the following:Basic vital signs including temperature, heart rate, respiratory rate, and blood pressure are measured once at screening, baseline, weeks 12 and 24.Laboratory tests including routine blood tests, liver function and kidney function tests are performed once at baseline, weeks 12 and 24.Adverse events (AEs) are evaluated and recorded on the case report form (CRF).

### Data management

2.10

In order to enhance participant retention and ensure complete follow-up, investigators contact participants by telephone to schedule and remind them of follow-up visits. This study utilizes an Electronic Data Capture (EDC) system and paper-based CRFs. The research center must maintain original source documents for all participants. Throughout the study, investigators or their designated clinical research coordinators enter source data into the EDC system in a timely and accurate manner. Following data entry and submission, the system performs automated logic checks. Subsequently, clinical monitors, data managers, and medical reviewers conduct multi-dimensional audits. Discrepancies identified during monitoring are electronically issued as queries to the originating personnel via the EDC system. After comprehensive verification by the principal investigator, statistician, and data manager, the study database will be permanently locked to preserve trial integrity, except under extraordinary circumstances requiring oversight by the ethics committee. The locked database will then be transferred to the statistical analysis team.

### Statistical analysis

2.11

The analysis will be performed using the intention-to-treat principle on the full analysis set, with additional analyses conducted on the per-protocol set and safety set. Only authorized study personnel will be able to view and manage data. The between-group comparison of acute exacerbation frequency will be conducted using a Poisson regression model that includes treatment group as the independent variable, annualized exacerbation rate as the dependent variable, and stratified randomization factors as adjustment covariates. Least squares means with corresponding 95% confidence intervals (with appropriate transformations when required) will be estimated from the specified model to evaluate between-group differences. Continuous variables will be analyzed using appropriate parametric (two-sample t-test or adjusted t-test) or nonparametric (Wilcoxon rank-sum test) methods, while categorical variables will be evaluated using either Pearson’s chi-square test or Fisher’s exact test. Time-to-event endpoints will be analyzed using Kaplan-Meier methodology, with median event times and interquartile ranges (IQR, 25th-75th percentiles) estimated for each group. Between-group differences will be assessed using log-rank tests. For missing data, the last observation carried forward method will be employed for imputation. For the center effect analysis, continuous variables will be analyzed using analysis of covariance or meta-analysis, while categorical variables will be assessed using Cochran-Mantel-Haenszel statistics.

Baseline demographic and clinical characteristics, including age, sex, disease duration, smoking status, smoking index, medical history, and concomitant medications, will be summarized descriptively and assessed for balance between groups. When appropriate, adjusted analyses will be conducted by including these variables as covariates in multivariable models to reduce the impact of potential confounding factors on treatment effect estimation. In addition, prespecified subgroup analyses stratified by sex will be performed to explore potential differences in treatment response to *Cordyceps militaris* capsules.

Safety analyses will be performed in the safety set, defined as all participants who receive at least one dose of study medication. The incidence of adverse drug reactions will be calculated based on events deemed certain, probable, and possible. Safety outcomes will be summarized by treatment group using the number and percentage of participants with any AE, adverse drug reaction or any SAE. Between-group comparisons of safety outcomes will be exploratory and conducted using Pearson’s chi-square test or Fisher’s exact test, as appropriate.

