### Study design

2.2

This is a multi-center, randomized, double-blind, parallel-group, placebo-controlled clinical trial. The trial has been initiated by the Guangdong Provincial Hospital of Chinese Medicine. After a 1-week run-in period, a total of 160 eligible participants are randomized to the treatment group (*Cordyceps militaris* capsules) or the control group (placebo capsules) in a 1:1 ratio. Participants receive a 24-week intervention and an additional 24-week follow-up period. Study visits will take place at baseline and weeks 12, 24, 36, and 48 within 30 days of each scheduled visit. Participants are required to provide written informed consent. The protocol follows the principles of the Standard Protocol Items: Recommendations for Interventional Trials (SPIRIT) Guidelines. A flowchart of the trial is shown in Figure 1. The schedule of enrollment, interventions, and assessments is presented in Table 1.

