#### Withdrawal/termination criteria

2.3.6

Participants are withdrawn from the trial if they meet any of the following criteria.Serious adverse events (SAEs) related to the investigational treatment occur.Serious complications, allergic reactions, clinically significant liver or kidney dysfunction, significant physiological changes that occur during the trial.Continued participation poses unacceptable risks to the participant, as judged by the principal investigator.Participants who experience recurrent infections during treatment will be withdrawn under the automatic withdrawal criteria. Specifically, if a participant experiences two or more acute exacerbations within 1 month requiring emergency department visits or hospitalization, the participant will be automatically withdrawn from the study to mitigate the risk of clinical deterioration and safeguard participant welfare.

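### The Poisson model for exacerbations takes the annualized rate, not the count with a follow-up offset, as its response; this understates the standard error and over-weights short follow-up

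*Protocol article*

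**What the plan says.** Section 2.11 (Statistical analysis) specifies, for acute exacerbation frequency, a "Poisson regression model that includes treatment group as the independent variable, annualized exacerbation rate as the dependent variable", with "stratified randomization factors as adjustment covariates". Under section 2.4 the only stratification factor is GOLD grade (I or II). The between-group result is to be read from this model as "Least squares means with corresponding 95% confidence intervals". The section names no count response, no exposure offset or weight, and no robust or scaled variance.

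The outcome is one of the secondary outcomes in section 2.8: "frequency of acute exacerbations, time to the first acute exacerbation".

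Four statements bear on follow-up time:
- Section 2.2: "Participants receive a 24-week intervention and an additional 24-week follow-up period", so 48 weeks in all.
- Section 2.2: visits may take place "within 30 days of each scheduled visit".
- Section 2.6: the sample size is raised "To accommodate an anticipated 15% attrition rate".
- Section 2.3.6: a participant is withdrawn automatically "if a participant experiences two or more acute exacerbations within 1 month requiring emergency department visits or hospitalization".

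Follow-up will therefore differ between participants, and for some it will be cut short by the outcome itself.

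**The concern.** A Poisson model ties the variance of its response to the mean. That holds for a count. It does not hold for a count divided by each participant's own follow-up and scaled up to a year. Doing so has two consequences.

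First, the model treats extrapolated events as if they had been observed. Follow-up is planned to be shorter than a year, so every rate is scaled up and the model credits itself with more information than was collected. The standard error even depends on the time unit. The same data expressed per month would give a standard error √12 ≈ 3.5 times as large.

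Second, each participant contributes one rate with equal weight, however long they were observed. A rate from a few weeks is far noisier than one from 48 weeks, but counts the same. The withdrawal rule in section 2.3.6 adds a route by which a participant with several events in a short time leaves early and enters with a very high rate.

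At stake are the confidence interval and the false-positive risk for a named secondary efficacy outcome.

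**Working it through.** The protocol gives no event rate, dispersion or power for exacerbations, so there is no stated figure to reproduce.

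**Inputs from the protocol:** 80 participants per group, 48 weeks of follow-up, 15% attrition. **Assumed:** true rates of 0.3, 0.6 and 1.0 per patient-year, equal in both groups; attrition spread uniformly from week 4, or from week 1, to week 48; 52.18 weeks per year. The stratum covariate is left out.

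**1. Variance.** If Y ~ Poisson(λT), with T in years, then Var(Y/T) = λ/T. A Poisson model on Y/T assumes λ. Hence

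model SE / true SE = 1/√mean(1/T), and type I error = 2[1 − Φ(1.96/√mean(1/T))].

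Neither expression depends on the event rate.

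- No dropout: T = 48/52.18 = 0.920, ratio √0.920 = 0.96, type I error 6.0%.
- 15% leave, uniform from week 4: mean(1/T) = 0.15 × ln(48/4)/44 × 52.18 + 0.85 × 52.18/48 = 0.442 + 0.924 = 1.366. Ratio 0.86, type I error 9.4%.
- 15% leave, uniform from week 1: mean(1/T) = 0.15 × ln(48)/47 × 52.18 + 0.924 = 0.645 + 0.924 = 1.569. Ratio 0.80, type I error 11.8%.

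**2. Simulation** (20,000 trials per setting, no treatment effect, no overdispersion, 48 weeks, 15% attrition):

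- Rate as response: type I error 8.7 to 11.0%.
- Count with offset log(T), same data: 4.5 to 4.8%.
- At 0.6/year with attrition from week 4, the rate response has mean model SE 0.207 against an empirical SD of 0.241 (type I error 8.9%). Count plus offset has 0.223 against 0.224 (4.7%).

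**3. Weight of early leavers** (48 weeks):

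- From week 4, mean follow-up of leavers is 26 weeks. Person-time share = 0.15 × 26/(0.15 × 26 + 0.85 × 48) = 8.7%. Share of the variance of the mean rate = 0.442/1.366 = 32%.
- From week 1, mean follow-up is 24.5 weeks. Person-time share 8.3%, variance share 0.645/1.569 = 41%.

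**4. Worst case under section 2.3.6.** Two events and withdrawal at week 4 give 2/(4/52.18) = 26.1/year. Two events over 48 weeks give 2.2/year. With 79 others at an assumed 0.6/year:

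- Rate as response: (79 × 0.6 + 26.09)/80 = 0.92/year.
- Count plus offset: (79 × 0.6 × 0.920 + 2)/(79 × 0.920 + 0.077) = 0.63/year.

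**5. Overdispersion, kept apart.** At 0.6/year with an assumed gamma dispersion of 1 and attrition from week 4, the rate response rejects in 15.8% and Poisson count plus offset, with model-based variance, in 11.0%. A good part of the inflation in that setting is therefore not due to the choice of response.

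**The case against.** The strongest defence is that the sentence is shorthand. A count model with a log follow-up offset gives annualized rates after back-transformation, and the section allows transformation of the least squares means. The article condenses a fuller plan, so the authors may have named the reported quantity, not the modelled one. That is possible. But the text expressly assigns the rate the role of dependent variable. An analysis plan that follows it inherits the error, and one that does not will contradict the published protocol. Either way the sentence needs correcting.

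Other objections stand, and limit the point:

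- A reader might infer that early leavers decide the comparison. They do not: under uniform dropout they carry about a third to two-fifths of the variance, which is over-weighting but not a majority.
- A reader might take the 26/year participant as typical. At 0.6 to 1.0 events/year the expected number per group of 80 with two or more events in the first 4 weeks is about 0.08 to 0.22, counting all severities, while the rule needs emergency or hospital care. Withdrawal at week 40 with two events gives 2/(40/52) = 2.6/year, close to a completer's 2.2. The simulations do not include the withdrawal rule.
- A reader might quote error rates of 15% or more. Over 48 weeks those require assumed overdispersion, under which the offset Poisson model is inflated too.
- The 15% in section 2.6 is a sample-size allowance with no timing attached.

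**Conclusion.** The specification is wrong as written and should be corrected, at moderate importance. With complete 48-week follow-up the harm is small: the standard error is about 4% too low and type I error is about 6%. With 15% attrition it is about 9 to 12%, against about 5% for count plus offset. That range rests on an assumed uniform dropout over 48 weeks and includes no overdispersion; the analytic values do not depend on the event rate. Overdispersion is a separate, additional source of inflation that a Poisson model with model-based variance does not cover.

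Two stronger readings are not supported. If only the 24-week treatment period were counted, the simulated error would be 21 to 24%, but the protocol does not fix that window and section 2.8 assesses the outcome through week 48. Nor does the flaw reach the trial's main conclusion: the outcome is secondary, the FEV1 analysis does not use this model, and the log-rank comparison of time to first exacerbation handles unequal follow-up by censoring.

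**What to change.** Replace the model sentence in section 2.11 with wording such as: the number of exacerbations per participant will be analysed by negative binomial regression (log link) with log follow-up time in years as offset and treatment group and GOLD grade as covariates; the rate ratio will be reported with its 95% confidence interval, and annualized rates per group will be derived from the model.

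Poisson regression on the count, with the same offset and a robust variance, is an acceptable alternative. A robust variance added to the present rate model would not be enough. It brings type I error back to about 5% (4.8 to 5.6% in simulation) but leaves the over-weighting of short follow-up.

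The cost is one sentence and a somewhat wider interval. At 0.6/year with attrition from week 4 and no overdispersion, the Poisson model SE on the log scale goes from 0.207 to 0.223 (0.223/0.207 = 1.08, about 8% wider). Allowing for overdispersion would widen it further if overdispersion is present. Section 2.3.1 expects recruitment to run to late 2026, so the change can be made before database lock. No clinical rule needs to change.

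### The only analysis stated that covers the primary FEV1 outcome is an open choice among a t-test, an undefined adjusted t-test and a Wilcoxon test, none said to adjust for baseline FEV1 or the GOLD stratum

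*Protocol article*

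**What the plan says.** Section 2.8 (Outcomes and measurements) states: "The primary outcome is change in the post-bronchodilator FEV_1". Section 2.6 (Sample size calculation) treats this as a comparison of means, "with an assumed mean difference of 110 mL between groups", with "standard deviations set at 250 mL for the treatment group and 201 mL for the control group".

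Section 2.4 (Randomization and allocation) says that "stratified block randomization was designed with airflow limitation severity (GOLD I and GOLD II) as the stratification factor". Section 2.3.2 defines those grades by post-bronchodilator FEV1 percent predicted.

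Section 2.11 (Statistical analysis) gives no model specific to FEV1. Its general rule is: "Continuous variables will be analyzed using appropriate parametric (two-sample t-test or adjusted t-test) or nonparametric (Wilcoxon rank-sum test) methods". The same section adjusts the Poisson model for exacerbation frequency for the stratification factor. It mentions analysis of covariance only for centre effects. After listing baseline characteristics to be described and checked for balance, it adds: "When appropriate, adjusted analyses will be conducted by including these variables as covariates in multivariable models". The list names age, sex, disease duration, smoking, medical history and medication. It names neither baseline FEV1 nor GOLD grade.

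**The concern.** The plan treats a secondary outcome more carefully than the primary one. The stratification factor is a cut of FEV1 percent predicted, so it bears most directly on FEV1, yet the only model said to include it is the one for exacerbations.

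Three things are at stake.

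- **Precision.** A change score uses baseline with a fixed coefficient of one. Regression on baseline estimates that coefficient and leaves less residual variance. Leaving out a balanced stratification factor tends to make the standard error too large.
- **What is estimated.** The sample size rests on a mean difference in mL, which a rank-sum test does not estimate. Moving between tests moves the target.
- **Error rate.** With no rule for choosing the test or the covariates, several results could be presented as the primary one.

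**Working it through.** **Inputs from Section 2.6.** Difference 110 mL; SDs 250 and 201 mL; "A one-sided superiority test is conducted with α = 0.025 and Power = 1-β = 0.90"; "assuming equal allocation between groups"; 68 evaluable per group; 80 per group after 15% attrition.

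**Assumed, not in the document.** The correlation ρ between baseline and follow-up FEV1, taken as 0.80 to 0.95, with equal variances at the two times.

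**1. The plan's own figure.** The sum of variances is 250² + 201² = 62,500 + 40,401 = 102,901, so the root-mean-square SD is √(102,901/2) = 226.8 mL. By normal approximation, n per group = (z₀.₉₇₅ + z_power)² × 102,901 / 110².

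- 90% power: 10.507 × 102,901 / 12,100 = 89.4, so 90 (91 with the unequal-variance t-test).
- 80% power: 7.849 × 102,901 / 12,100 = 66.7, so 67 (68 with the unequal-variance t-test).

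The stated 68 therefore matches 80% power, not 90%. The attrition step does reproduce: 136/0.85 = 160. The power shortfall is a separate matter; it matters here only because it sets the starting point for the comparison below.

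**2. Gain from adjusting for baseline FEV1.** With common variance σ², Var(change) = 2σ²(1−ρ), and the residual variance after regression on baseline is σ²(1−ρ²). The ratio is (1+ρ)/2. Unequal-variance t power at 110 mL, one-sided 0.025:

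| Analysis | Variance ratio | SE reduction | Power, 68 per group | Power, 80 per group |
|---|---|---|---|---|
| Unadjusted change | 1.000 | none | 80.1% | 86.2% |
| ANCOVA, ρ = 0.95 | 0.975 | 1.3% | 81.1% | 87.0% |
| ANCOVA, ρ = 0.90 | 0.950 | 2.5% | 82.1% | 87.8% |
| ANCOVA, ρ = 0.80 | 0.900 | 5.1% | 84.1% | 89.5% |

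For 90% power, the requirement falls from 91 per group to 89 (ρ = 0.95) or 82 (ρ = 0.80), a saving of 2 to 9 per group.

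At 80 per group the unadjusted SE is √(102,901/80) = 35.9 mL, a 95% half-width of about 1.96 × 35.9 = 70 mL. Adjustment brings it to about 67 to 69 mL.

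**3. Which end of the range fits.** A change SD of 226.8 mL implies a cross-sectional SD of 226.8/√(2(1−ρ)): 359 mL at ρ = 0.80, 507 mL at 0.90 and 717 mL at 0.95. The document gives no cross-sectional SD against which to check these.

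**4. Wilcoxon.** Under normality its relative efficiency is 3/π, so the effective variance is multiplied by π/3. Power is about 78.3% at 68 per group and 84.6% at 80.

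**5. Open choice.** In a null simulation (20,000 runs, 68 per group, ρ = 0.9, nominal one-sided 2.5%), rejection rates were 2.5% for the t-test, 2.4% for Wilcoxon and 2.5% for ANCOVA, each used alone. Taking the better of t and Wilcoxon gave 2.96%. Taking the best of all three gave 3.4%.

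**Not quantified.** What GOLD grade adds once baseline FEV1 is in the model; the document gives nothing from which to derive it.

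**The case against.** The strongest reply is that this is a journal article. The quoted sentence is generic, and a full protocol or SAP may name a primary model. That silence alone would be no finding. But the article does state a method that covers the primary outcome, and it does specify stratum adjustment for a secondary one. The criticism is of what is stated, and it stands on that footing.

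Four stronger readings are tempting, and the text does not support them.

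- **That the analysis ignores baseline FEV1.** The endpoint is a change, so baseline is already subtracted. Only covariate adjustment is missing.
- **That the estimate is biased by regression to the mean or by omitting the stratum.** Under randomization the unadjusted difference in change is unbiased, and omitting a balanced stratum is conservative. A hypothetical chance baseline difference of 50 mL would shift a particular estimate by (1−ρ) × 50, that is 10 to 2.5 mL. That is conditional on the imbalance and small beside 110 mL.
- **That adjustment is triggered by observed imbalance.** The balance check comes just before the sentence on adjusted analyses, but no trigger is stated. The condition is simply undefined.
- **That baseline FEV1 and GOLD grade are excluded as covariates.** The list is illustrative. Neither is named and neither is ruled out.

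It is also fair to say that the precision gain is small. The error inflation is a worst case, because it assumes that the most favourable result would be chosen. The adjusted t-test is undefined; it most likely means the unequal-variance test, but the article does not say so.

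**Conclusion.** The point holds in a limited form. As stated, the primary comparison is an open choice of tests with no named adjustment for baseline FEV1 or the randomization stratum, and this is inconsistent with the exacerbation model.

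The result would be valid but less precise than it could be. For ρ between 0.95 and 0.80 with equal variances, the gain from baseline adjustment is 2.5% to 10% of variance, or about 1 to 4 points of power. Both conditions are assumptions. The open choice of test matters as much: it leaves the estimated quantity unsettled and permits an error rate of about 3.0% to 3.4% against 2.5% if the best result were picked.

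A reader might infer that missing covariates explain why power at 68 per group is 80.1% rather than the stated 90%. They do not: baseline adjustment over the assumed range recovers only 1 to 4 of those points.

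This should be corrected, but it does not threaten the trial's validity.

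**What to change.** Name one primary analysis in Section 2.11: ANCOVA of change in post-bronchodilator FEV1 at the primary time point, with treatment, baseline post-bronchodilator FEV1 and GOLD stratum as terms, and a robust variance because the assumed SDs differ. Section 2.8 lists weeks 12, 24, 36 and 48 without marking one as primary, so the same sentence should name it. Report the adjusted mean difference in mL with its 95% CI. Keep the t-test, the Wilcoxon test and any other covariate sets as sensitivity analyses, fixed in advance.

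The cost is wording only. Baseline spirometry is scheduled, and GOLD grade is known at randomization. Section 2.3.1 expects recruitment to run to late 2026, so on that schedule the change can be made before database lock and unblinding.
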